### **5.3 Vaccine Storage**

Pfs25-EPA/Alhydrogel® vaccines are stored at 2-8 °C and may NOT be frozen at any time. Refrigerator temperature will be continuously monitored using an alarm system.

### **5.4 Vaccine Accountability**

After administration of a vaccine dose, the single-dose vial will be returned to the storage facility at the test site, and vials will be accounted for and stored until monitoring by the IND Sponsor. The used vials may then be disposed of according to site standard operating procedures after monitoring has been completed.

The trial site pharmacist is responsible for maintaining an accurate inventory and accountability record of vaccine supplies for this study. Partially used vials may not be administered to other subjects.

## **6 Study Procedures**

### **6.1 Screening**

The purpose of the screening visit (as described in Section 4.2) is to determine volunteer eligibility for study participation. Subjects who are diagnosed with a medical condition during the screening process (e.g., test positive for hepatitis B, hepatitis C, or HIV) will be notified and referred for medical care when possible according to Maryland reporting requirements.

The following screening procedures and evaluations for this study must be completed within 60 days prior to first vaccination.

- Explain the study and Informed Consent to the subject.
- Ensure the subject has successfully completed the Informed Consent Comprehensive Exam, has signed the Informed Consent and receives a signed copy of the Informed Consent

- Ensure that HIV pre-test counseling has been performed and ensure that the subject has agreed to HIV testing (required by Maryland state law).
- Elicit a complete medical history, including menstrual and contraceptive history and/or history of surgical sterility for females.
- Pregnancy prevention counseling will be performed.
- Administer a complete physical examination, including vital signs (height, weight, blood pressure, temperature, respirations, and pulse).
- Obtain a signed medical release of information form from the patient.
- Obtain approximately 20 mL of blood for complete blood count (CBC) with differential and platelet count, ALT, creatinine, hepatitis B surface antigen, hepatitis C antibody, HIV antibody.
- Obtain urine for pregnancy testing and dipstick testing for protein and blood.

## **6.2 Assignment to Groups**

Subjects in Group 1a will be enrolled first, followed by Group 1b, and Group 2. (Note: subjects in Group 2 were initially randomly assigned to a 2 or 3 dose vaccination schedule (Group 2a or 2b); the protocol was subsequently amended (Version 3) such that all subjects in Group 2 receive 3 doses of vaccine). The protocol was again amended (Version 4) so that the subjects in Group 2 can receive an additional booster 6-8 months later if they received at least 2 previous doses of the vaccine, and so that subjects in Group 1 can also receive the booster 8-9 months later if they had an exceptionally high antibody titer response to the first 2 doses (>500 EU).

## **6.3 Immunization Procedure**

Vaccines will be administered IM in the deltoid muscle. Arms may be alternated with successive vaccinations.

## **6.4 Clinical Monitoring and Evaluation**

The study schedule and approximate amounts of blood drawn are summarized in [Appendix B](#).

### **All Groups**

#### **Study Day 0 (Day of First Vaccination)**

1. Verify that Informed Consent was obtained.
2. Ensure that all inclusion/exclusion criteria are met.
3. Ensure that CBC, ALT, and creatinine measurements from screening tests are within protocol-defined limits ([Section 4.4](#) Exclusion Criteria) before vaccinating.
4. Perform interim history and physical examination, focusing on any acute complaints.
5. Obtain blood for CBC with differential and platelet count, ALT, creatinine, anti-Pfs25 antibody ELISA, SMFA, and B and T cell studies.
6. Obtain a urine sample for dipstick testing and ensure that protein and blood are no more than

trace positive before vaccinating. Should a female subject have more than trace blood in her urine on Day 0, she will not be excluded from vaccination if she is currently menstruating.

7. For females, obtain a urine or serum sample for  $\beta$ -hCG testing. Ensure that the test is negative before vaccinating; a positive test will exclude the subject from the trial. Pregnancy prevention counseling will be performed.
8. Record vital signs (blood pressure, temperature, heart rate, and respiratory rate).
9. Administer the vaccine.
10. Observe for at least 30 minutes after vaccination to evaluate for immediate adverse reactions.
11. Education by study staff during 30-minute post-immunization wait period, describing proper use of digital thermometer, injection-site reaction measurement, and malaria vaccine side-effect memory enhancement card. Study staff will also discuss signs and symptoms of potential AEs, and indications for use of antipyretics (acetaminophen or ibuprofen) if fever, headache, or malaise occurs.

### **Study Day 3 $\pm$ 1 Day**

1. Perform basic history and focused physical examination (including injection site), emphasizing examination of any acute complaints.
2. Review memory enhancement card.
3. Record vital signs.
4. Obtain blood for CBC with differential and platelet count, ALT, and creatinine.

### **Study Day 7 $\pm$ 1 Day**

1. Perform basic history and focused physical examination (including injection site), emphasizing examination of any acute complaints.
2. Record vital signs.
3. Obtain blood for CBC with differential and platelet count.
4. Obtain urine for dipstick testing.
5. Review Days 0-6 memory enhancement card.

### **Study Day 14 $\pm$ 2 Days**

1. Perform basic history and focused physical examination (including injection site), emphasizing examination of any acute complaints.
2. Record vital signs.
3. Obtain urine for dipstick testing. Obtain urine or serum for  $\beta$ -hCG testing.
4. Obtain blood for CBC with differential and platelet count, ALT, creatinine, anti-Pfs25 antibody ELISA.
5. Review pregnancy prevention counseling.

### **Study Day 28 $\pm$ 3 Days**

1. Perform directed history and assessment of any physical complaint.
2. Record vital signs.
3. Obtain urine for dipstick testing.
4. Review pregnancy prevention counseling.

**Study Day 56 +14 (Day of Second Vaccination)**

1. Perform basic history and focused physical examination, emphasizing examination of any acute complaints.
2. Review criteria for vaccination.
3. Obtain blood for CBC with differential and platelet count, ALT, creatinine, anti-Pfs25 antibody ELISA, and B and T cell studies.
4. For females, obtain a urine or serum sample for  $\beta$ -hCG testing. Ensure that the test is negative before vaccinating; a positive test will exclude the subject from the trial. Pregnancy prevention counseling will be reviewed.
5. Obtain a urine sample for dipstick testing and ensure that protein and blood are no more than trace positive before vaccinating. Should a female subject be menstruating on Day 56, she will not be excluded from vaccination if she has more than trace blood in her urine.
6. Record vital signs (blood pressure, temperature, heart rate, and respiratory rate).
7. Administer the vaccine.
8. Observe for at least 30 minutes after vaccination to evaluate for immediate adverse reactions.
9. Review of proper use of digital thermometer, injection-site reaction measurement tool, and memory enhancement card (diary) by study staff during 30-minute post-immunization wait period. Study staff will also discuss signs and symptoms of potential AEs, and indications for use of antipyretics (acetaminophen or ibuprofen) if fever, headache, or malaise occurs.

**Study Day 59  $\pm$ 1 Day (3 Days after Second Vaccination)**

1. Perform basic history and focused physical examination (including injection site), emphasizing examination of any acute complaints.
2. Review memory enhancement card.
3. Record vital signs.
4. Obtain blood for CBC with differential and platelet count, ALT, and creatinine.

**Study Day 63  $\pm$ 1 Day (7 Days after Second Vaccination)**

1. Perform basic history and focused physical examination (including injection site), emphasizing examination of any acute complaints.
2. Record vital signs.
3. Review memory enhancement card.
4. Obtain urine for dipstick testing.
5. Obtain blood for CBC with differential and platelet count, and B and T cell studies.

**Study Day 70  $\pm$ 2 Days (14 Days after Second Vaccination)**

1. Perform basic history and focused physical examination (including injection site), emphasizing examination of any acute complaints.
2. Record vital signs.
3. Obtain urine for dipstick testing. Obtain urine or serum for  $\beta$ -hCG testing.
4. Obtain blood for CBC with differential and platelet count, ALT, creatinine, anti-Pfs25 antibody ELISA, B and T cell studies, and SMFA.
5. Review pregnancy prevention counseling.

**Study Day 84  $\pm$ 3 Days (28 Days after Second Vaccination)**

1. Perform basic history and assessment of any physical complaint.
2. Record vital signs.
3. Obtain urine for dipstick testing.
4. Review pregnancy prevention counseling.

**Groups 1(a and b)****Study Day 120  $\pm$ 7 Days**

1. Perform directed history and assessment of any physical complaint.
2. Record vital signs.
3. Obtain urine for dipstick testing.

**Study Day 180  $\pm$ 14 Days**

1. Perform directed history and assessment of any physical complaint.
2. Record vital signs.
3. Obtain urine for dipstick testing.
4. Obtain approximately 5 mL of blood for anti-Pfs25 ELISA.

**Study Day 270  $\pm$ 14 Days**

1. Perform directed history and assessment of any physical complaint.
2. Record vital signs.
3. Obtain approximately 5 mL of blood for anti-Pfs25 ELISA.

**Study Day 420  $\pm$ 14 Days**

1. Perform directed history and assessment of any physical complaint.
2. Record vital signs.
3. Obtain blood for anti-Pfs25 ELISA, and T and B cell studies.

**Group 2****Study Day 120  $\pm$ 28 Days (Day of Third Vaccination)**

1. Perform basic history and focused physical examination, emphasizing examination of any acute complaints.
2. Review criteria for vaccination.
3. Obtain blood for CBC with differential and platelet count, ALT, creatinine, anti-Pfs25 antibody ELISA, and B and T cell studies.
4. For females, obtain a urine or serum sample for  $\beta$ -hCG testing. Ensure that the test is negative before vaccinating; a positive test will exclude the subject from the trial. Review pregnancy prevention counseling.
5. Obtain a urine sample for dipstick testing and ensure that protein and blood are no more than trace positive before vaccinating. Should a female subject be menstruating on the day of vaccination, she will not be excluded from vaccination if she has more than trace blood in her urine.

6. Record vital signs (blood pressure, temperature, heart rate, and respiratory rate).
7. Administer the vaccine.
8. Observe for at least 30 minutes after vaccination to evaluate for immediate adverse reactions.
9. Review of proper use of digital thermometer, injection-site reaction measurement tool, and memory enhancement card (diary) by study staff during 30-minute post-immunization wait period. Study staff will also discuss signs and symptoms of potential AEs, and indications for use of antipyretics (acetaminophen or ibuprofen) if fever, headache, or malaise occurs.

**Study Day 123  $\pm$ 1 Day (3 Days after Third Vaccination)**

1. Perform basic history and focused physical examination (including injection site), emphasizing examination of any acute complaints.
2. Review memory enhancement card.
3. Record vital signs.
4. Obtain blood for CBC with differential and platelet count, ALT, and creatinine.

**Study Day 127  $\pm$ 1 Day (7 Days after Third Vaccination)**

1. Perform basic history and focused physical examination (including injection site), emphasizing examination of any acute complaints.
2. Record vital signs.
3. Review memory enhancement card.
4. Obtain urine for dipstick testing.
5. Obtain blood for CBC with differential and platelet count, and B and T cell studies.

**Study Day 134  $\pm$ 2 Days (14 Days after Third Vaccination)**

1. Perform basic history and focused physical examination (including injection site), emphasizing examination of any acute complaints.
2. Record vital signs.
3. Obtain urine for dipstick testing. Obtain urine or serum for  $\beta$ -hCG testing.
4. Obtain blood for CBC with differential and platelet count, ALT, creatinine, anti-Pfs25 ELISA, B and T cells, and SMFA.
5. Review pregnancy prevention counseling.

**Study Day 148  $\pm$ 3 Days (28 Days after Third Vaccination)**

1. Perform basic history and assessment of any physical complaint.
2. Record vital signs.
3. Obtain urine for dipstick testing.
4. Review pregnancy prevention counseling.
5. Obtain blood for anti-Pfs25 ELISA

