**Study Day 270 ±14 Days**

1. Obtain informed consent for Version 4, if subject is willing.
2. Perform directed history and assessment of any physical complaint.
3. Record vital signs.
4. Obtain blood for CBC with differential and platelet count.
5. Obtain urine for dipstick testing.
6. For females, obtain urine for  $\beta$ -hCG testing.
7. Obtain blood for anti-Pfs25 ELISA.

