| VACCINATION                   |                           |     |    | X |     |     |                |    | X |     |     |     |    |     |     |                  |     |
| Pfs25-EPA ELISA                      | 5 mL                      |     |    | X        |     |     | X              |    | X        |     |     | X   |    |     | X   | X                | X   |
| Membrane feeding assay   | 20 mL                     |     |    | X        |     |     |                |    |          |     |     | X   |    |     |     |                  |     |
| T & B cell analysis      | 40 mL                     |     |    | X        |     |     |                |    | X        |     | X   | X   |    |     |     |                  | X   |
| Daily blood draw                     |                           |     | 20 | 75       | 10  | 5   | 15             |    | 55       | 10  | 45  | 75  |    |     | 5   | 5                | 45  |
| Cumulative Blood Volume in mL |                           |     | 20 | 95       | 105 | 110 | 125            |    | 180      | 190 | 235 | 310 |    |     | 315 | 320              | 365 |

Total blood volume to drawn over course of study is 365 mL for Groups 1(a and b) who receive 2 doses, 500 mL for those who get the optional booster dose, 700 mL for Group 2.

With large volume blood draws totals are up to 900 and 1500 mL respectively.

CBC parameters to be assessed for safety: WBC, absolute neutrophil count, hemoglobin, and platelet count.

Days of second and third vaccinations can range according to the specified window, in which case subsequent follow-up should be adjusted accordingly (i.e., Day 1 after second vaccine instead of Day 57, etc.)

Plasma remaining from T and B cell studies will be stored and may be used for transmission blocking assays.

 Subjects with exceptionally high antibody titers after the second dose will be offered an optional booster dose. If they accept, their study schedule changes to the one below.

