| Cumulative Blood Volume in mL |                           |       | 325 | 380      | 390 | 390 | 465 | 470 | 495 | 500 | 505 | 550 |

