| HbsAg & HCV
ELISA                         | 5 mL                      |       | X  |          |     |     |     |   |                |     |     |     |    |                |     |     |     |     |     |     |     |
| VACCINATION                           |                           |       |    | X |     |     |     |   | X       |     |     |     |    | X       |     |     |     |     |     |     |     |
| Pfs25-EPA
ELISA                           | 5 mL                      |       |    | X        |     |     | X   |   | X              |     |     | X   |    | X              |     |     | X   | X   | X   | X   | X   |
| Membrane
feeding assay        | 20 mL                     |       |    | X        |     |     |     |   |                |     |     | X   |    |                |     |     | X   |     |     |     |     |
| T & B cell
analysis           | 40 mL                     |       |    | X        |     |     |     |   | X              |     | X   | X   |    | X              |     |     | X   |     |     |     | X   |
| Daily blood draw                             |                           |       | 20 | 75       | 10  | 5   | 15  |   | 55             | 10  | 45  | 75  |    | 55             | 10  | 5   | 75  | 5   | 5   | 5   | 45  |
| Cumulative
Blood Volume in
mL |                           |       | 20 | 95       | 105 | 110 | 125 |   | 180            | 190 | 235 | 310 |    | 365            | 375 | 380 | 455 | 460 | 465 | 470 | 515 |

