| VACCINATION                   |                           |       |     | X |     |     |     |    | X |     |     |     |    | X |     |     |     |     |     |     |
| Pfs25-EPA ELISA                      | 5 mL                      |       |     | X        |     |     | X   |    | X        |     |     | X   |    | X        |     |     | X   |     | X   | X   |
| Membrane feeding assay   | 20 mL                     |       |     | X        |     |     |     |    |          |     |     | X   |    |          |     |     | X   |     |     |     |
| T & B cell analysis      | 40 mL                     |       |     | X        |     |     |     |    | X        |     | X   | X   |    | X        |     | X   | X   |     |     |     |
| Daily blood draw                     |                           |       | 20  | 75       | 10  | 5   | 15  |    | 55       | 10  | 45  | 75  |    | 55       | 10  | 5   | 75  |     | 5   | 10  |
| Cumulative Blood Volume in mL |                           |       | 20  | 95       | 105 | 110 | 125 |    | 180      | 190 | 235 | 310 |    | 365      | 375 | 380 | 455 |     | 460 | 470 |

|                                      |                           | Month | 10       |     |     |     | 11  | 12  | 15  | 18  | 22  |
|--------------------------------------|---------------------------|-------|----------|-----|-----|-----|-----|-----|-----|-----|-----|
| Procedures                           | Blood Volume  | Day   | 300      | 303 | 307 | 314 | 328 | 356 | 450 | 540 | 660 |
| Complete History/Physical            |                           |       |          |     |     |     |     |     |     |     |     |
| Obtain Informed Consent              |                           |       |          |     |     |     |     |     |     |     |     |
| Interim Clinical Evaluation          |                           |       | X        | X   | X   | X   | X   | X   | X   | X   | X   |
| CBC                      | 5 mL                      |       | X        | X   |     | X   |     |     |     |     |     |
| ALT/Creatinine                       | 5 mL                      |       | X        | X   |     | X   |     |     |     |     |     |
| Urine dipstick test                  |                           |       | X        |     | X   | X   | X   | X   | X   | X   |     |

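### Section 6.4 and the two Appendix B tables for Group 2 conflict on the Day 127 T/B-cell and Day 148 ELISA samples, and several stated blood volumes do not follow from the schedule

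*Protocol*

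**What the plan says.** Section 6.4 has a single Group 2 visit list up to Day 270, with no distinction by booster status.

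- Day 127 (7 days after dose 3): "Obtain blood for CBC with differential and platelet count, and B and T cell studies".
- Day 148 (28 days after dose 3): "Obtain blood for anti-Pfs25 ELISA".
- Day 270: "Obtain informed consent for Version 4, if subject is willing". The same visit also lists "Obtain blood for CBC with differential and platelet count", and an ELISA sample.

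Appendix B covers the same period twice, once for Group 2 subjects without the booster and once for those with it. In the no-booster table the T/B row is ticked at Days 120, 134 and 480 and blank at Day 127, and the ELISA row is ticked at Day 148. In the booster table the "T & B cell analysis" row is ticked at Day 127, and the ELISA row is blank at Day 148. Both tables print a 5 mL draw for Day 127.

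Footnote 1 gives 365 mL for Group 1 without a booster, then "500 mL for those who get the optional booster dose, 700 mL for Group 2". With large-volume draws it gives up to 900 and 1,500 mL. The cumulative row of the Group 1 booster table ends "495 | 500 | 505 | 550". That of the no-booster Group 2 table ends "375 | 380 | 455 | 460 | 465 | 470 | 515".

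**The concern.** At Days 127 and 148 a Group 2 subject has no booster status, because the booster is first put to subjects at Day 270. Two tables that differ at those visits therefore cannot both be applied, and neither reproduces Section 6.4 at both visits.

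The effect of the third and booster doses on antibody is a secondary objective. A site working from the booster table would not draw the 28-day post-dose-3 ELISA. A site working from the no-booster table would not draw the 7-day post-dose-3 T/B sample, whose post-dose-2 counterpart (Day 63) is taken in everyone. If sites differed in practice, these samples would be missing because of which page was followed and not because of anything about the subject.

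The volumes matter separately. Footnote 1 is the protocol's own statement of total blood drawn, and for boosted subjects it is below what the schedule requires.

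**Working it through.** **Inputs.** Appendix B volumes per test: CBC 5 mL, ALT/creatinine 5, HIV 5, HBsAg/HCV 5, ELISA 5, membrane feeding 20, T/B cells 40. Section 6.5: up to 400 mL per large-volume draw, after the third and/or last vaccination.

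**1. The visits side by side (Group 2).**

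| Visit | Section 6.4 | No-booster table | Booster table |
|---|---|---|---|
| Day 127 T/B cells | yes | no | yes |
| Day 127 draw implied or printed | 45 mL | 5 mL | 5 mL |
| Day 148 ELISA | yes | yes | no |
| Day 270 CBC | yes | no | yes |

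The blank Day 148 cell is not an artefact of a broken table. The booster table's cumulative row goes 455, blank, 460 across Days 134, 148 and 175, whereas the no-booster row goes 455, 460, 465.

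**2. Reproduce the printed totals.** Screening to Day 70, common to all groups: 20+75+10+5+15+55+10+45+75 = 310 mL. Booster phase, Days 300 to 660: 55+10+0+75+5+25+5+5+45 = 225 mL.

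- Group 1, no booster: 310+5+5+45 = 365. Agrees with footnote 1.
- Group 1, booster: 310+5+10+225 = 550. Agrees with its table; footnote 1 says 500.
- Group 2, no booster: 310+55+10+5+75+5+5+5+45 = 515. Agrees with its table.
- Group 2, booster: 310+55+10+5+75+5+10+225 = 695. Agrees with its table; footnote 1 says 700.

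**3. Ticks times volumes.** Group 2 booster, Day 127: CBC 5 + T/B 40 = 45 mL, but 5 mL is printed. The same pair of tests on Day 63 is printed as 45 mL in the same table. Total from the table's own ticks: 695+40 = 735 mL. In the other three tables the ticks reproduce the printed totals.

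**4. Totals under Section 6.4.**

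- Group 2, booster: 735 + 5 (Day 148 ELISA) = 740 mL. The table is 45 low and the footnote 40 low.
- Group 2, no booster: 515 + 40 (Day 127 T/B) + 5 (Day 270 CBC) = 560 mL. The table is 45 low. If the Day 270 CBC is not required in these subjects the total is 555 mL and the gap is 40.
- Group 1, booster: the table's 550 mL includes a Day 270 CBC that the Group 1 Day 270 visit in Section 6.4 does not list. Without it, 550−5 = 545 mL. Footnote 1 is 50 or 45 low.

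**5. With large-volume draws.** The footnote's figures are reproduced by 500+400 = 900 (one draw, Group 1) and 700+2×400 = 1,500 (two draws, Group 2). On the corrected bases these become 550+400 = 950 mL (545+400 = 945 by Section 6.4) and 740+800 = 1,540 mL.

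**The case against.** Several things limit this point.

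- Section 6.4 describes the Appendix B volumes as approximate, and the protocol states no blood-volume ceiling. The boosted Group 2 gap is 45 mL in 740 (about 6%) over 22 months. A reader might infer that a safety limit is breached; nothing in the document supports that. The large draws are optional and fall under a separate protocol and consent. This stands, and it keeps the volume errors modest.
- A reader might infer that every stated total is too low. That is not so. The 365 mL for unboosted Group 1 is correct. The 515 mL for unboosted Group 2 matches that table's own ticks and is low only against Section 6.4. The footnote's 700 mL for Group 2 exceeds 560 mL, so it does not understate the unboosted subjects.
- A reader might infer that the comparison of post-dose-3 with post-booster antibody is lost. The protocol does not specify a Day 148 versus Day 328 comparison. Section 11.3 names ELISA on vaccination days, 2 weeks after each vaccination and periodically, and the 14-day samples at Days 134 and 314 are ticked in the booster tables. Day 134 T/B cells are ticked in both Group 2 tables.
- Version 6.0 is dated 9 January 2013. With accrual around September 2011, Group 2 would have reached Day 148 in early 2012, so correcting the tables may recover no sample. That is probably true. It changes what the correction is for, but the document still has to say what was required.
- The two tables might be read as a deliberate difference in sampling. The single list in Section 6.4, the Day 270 consent and the booster table's conflict with its own volume on Day 127 all speak against that.

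**Conclusion.** The inconsistency is real and lies entirely within the document; it is not a design choice. Followed literally, Appendix B removes one secondary-endpoint time point (28-day post-dose-3 ELISA) from boosted subjects or one exploratory time point (7-day post-dose-3 T/B cells) from unboosted subjects. The planned test of dose effect, which uses antibody 2 weeks after the second vaccination, the sample size and the primary safety endpoint are unaffected.

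Two volume errors need no choice between sections: 5 mL printed against 45 mL ticked on Day 127 in the booster table, and 500 mL in footnote 1 against 550 mL in the Group 1 booster table. The remaining differences are relative to Section 6.4, and 5 mL of each of the 560 and 550 mL figures depends on how the Day 270 CBC is resolved. The large-draw totals assume two 400 mL draws in Group 2 and one in Group 1, the only counts that reproduce the footnote from its own base figures.

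**What to change.** Replace the two Group 2 tables with one schedule through Day 270 that matches Section 6.4 (T/B cells on Day 127 and ELISA on Day 148 for everyone), and split by booster status only after that visit. Where these visits have already taken place, correct the tables to show what was required and what was collected, so that missing samples are not taken for planned omissions.

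Reconcile the Day 270 CBC in both directions: Section 6.4 lists it for Group 2 but the no-booster table does not, and the Group 1 booster table lists it but the Group 1 visit in Section 6.4 does not.

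Then restate the volumes:

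| Subjects | Stated (mL) | Restated (mL) |
|---|---|---|
| Group 2, booster | 695 (table), 700 (footnote) | 740 |
| Group 2, no booster | 515 (table) | 560, or 555 without the Day 270 CBC |
| Group 1, booster | 550 (table), 500 (footnote) | 550, or 545 without the Day 270 CBC |
| Group 2 with large draws | 1,500 | 1,540 |
| Group 1 with large draw | 900 | 950, or 945 without the Day 270 CBC |

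The cost is a correction to the tables and footnote. It asks for no T/B or ELISA sample beyond those already in Section 6.4.
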